**Supplementary material**

**Supplementary Figure 1 CONSORT Flow Diagram**

Allocation

Suitable samples for analysis (n = 14)

Lost to follow up (n = 0)

Enrolment

Suitable samples for analysis (n = 14)

Lost to follow up (n = 0)

Allocated to control PBMF (n = 15)

- Received allocated intervention (n = 15)
- No informative samples (n=1)

Analysis

Randomized (n = 31)

Assessed for eligibility (n = 50)

Follow up

Excluded (n = 19)

- Declined to participate (n = 17)
- Not approached (n = 2)

Allocated to intervention PHMF (n = 16)

- Study stopped before intervention commenced (n = 1)
- Clinician lost equipoise (n = 1)
- Received allocated intervention

(n =14)

**Supplementary Table 1** Number of stool samples analysed by group and time point

| Sample details | PBMF (14) | PHMF (14) | Median day of study (IQR) |
| --- | --- | --- | --- |
| Enrolment | 14 | 13 | 0 (0-0) |
| Day seven | 14 | 14 | 7 (7-8) |
| Day 14 | 3 | 1 | 14 (14-14_ |
| Day 21 | 9 | 13 | 21 (21-22) |
| Discharge | 7 | 10 | 29 (37-45) |

**Supplementary Table 2** Plasma amino acid concentrations on day seven and day 21 by study group

| **Amino acid reference intervals (µmol/L)**  **18)** | **Control PBMF**  **Median (IQR) [% outside ref range]** | | **Intervention PHMF**  **Median (IQR) [% outside ref range]** | |
| --- | --- | --- | --- | --- |
|  | **Day 7 (n=12)** | **Day 21 (n=7)** | **Day 7 (n=12)** | **Day 21 (n=13)** |
| Alanine(208– 588)  1 wk to < 19 yrs | 217 (182-352)  [41] | 317 (238-35)  [14] | 317 (238-335)  [17] | 298 (201-390)  [23] |
| α-amino Butyric acid (8-30)1 wk to < 19 yrs | 4 (0-6)  [88] | 7 (3-12)  [50] | 4 (2-5)  [100] | 4 (2-6)  [100] |
| Arginine (47–138)  1 month to < 1 yr | 58 (35-67)  [33] | 70 (43-82)  [28] | 75 (55-84)  [17] | 57 (47-85)  [23] |
| Asparagine (38–91)  0 to < 19 yrs | 72 (58-121)  [17] | 73 (52-117)  [20] | 75 (64-88)  [14] | 69 (65-90)  [15] |
| Aspartate (20–42)  2 wks to < 19 yrs | 6 (6-14)  [77] | 6 (5-28)  [80] | 8 (7-39)  [72] | 7 (6-13)  [86] |
| Citrulline (9 – 44)  0 to < 1 yr | 19 (16-26)  [0] | 20 (17-31)  [14] | 19 (15-23)  [0] | 23 (18-16)  [8] |
| Cystine(3 – 20)  2 wks to < 8 yrs | 25 (23-30)  [88] | 24 (23-28)*  [100] | 31 (26-35)  [100] | 32 (25-40)*  [100] |
| Glutamate (74–266)  2 wks to < 1 yr | 50 (41-75)*  [69] | 64 (45-104)  [57] | 92 (54-136)*  [31] | 84 (50-110)  [46] |
| Glutamine (332–789)  1 wk to < 1 yr | 370 (307-572)  [17] | 449 (335-622)  [14] | 443 (335-622)  [34] | 458 (323-570)  [15] |
| Glycine (196 – 398)  2 wks to < 13 yrs | 184 (173-193)*  [83] | 190 (187-226)  [57] | 215 (191-317)*  [34] | 187 (124-224)  [59] |
| Histidine (65-113) 2 wks to < 19 yrs | 83 (59-120)  [58] | 90 (57-180)  [71] | 114 (85-144)  [50] | 110 (71-155)  [62] |
| Isoleucine (30 – 113)  2 wks to < 1 yr | 62 (49-82)  [17] | 58 (51-62)  [0] | 54 (46-66)  [0] | 53 (43-64)  [8] |
| Leucine (55 – 188)  1 wk to < 1 yr | 90 (75-131)  [0] | 89 (85-116)  [0] | 103 (79-124)  [0] | 97 (76-119)  [0] |
| Lysine (102 – 259)  2 wks to < 19 yrs | 185 (147-214)  [33] | 159 (73-195)  [43] | 137 (63-213)  [58] | 72 (62 – 207)  [59] |
| Methionine (13–44)  0 to < 19 yrs | 26 (21-33)  [17] | 28 (22-30)  [0] | 24 (18-31)  [8] | 25 (19-34)  [0] |
| Ornithine (40–132)  2 wks to < 1 yr | 99 (85-125)  [8] | 99 (95-132)  [14] | 133 (95-200)  [42] | 105 (79-137)  [23] |
| Phenylalanine  (52–116)2wks to<1 yr | 46 (41-55)  [42] | 50 (43-53)  [71] | 50 (43-59)  [58] | 40 (37-56)  [70] |
| Proline (127–292)  0 to < 1 yr | 180 (142-219)  [25] | 191 (129-229)  [14] | 168 (139-221)  [0] | 175 (142-206)  [15] |
| Serine (112 – 216)  2 wks to < 19 yrs | 128 (113-147)  [25] | 141 (120-159)  [28] | 168 (125-263)  [50] | 124 (101-155)  [15] |
| Taurine (55 – 204)  2 wks to < 19 yrs | 84 (51-104)  [25] | 94 (59-136)  [14] | 100 (74-152)  [8] | 74 (50-93)  [31] |
| Threonine (27–187)  2 wks to < 19 yrs | 251 (190-308)*  [75] | 210 (171-241)*  [57] | 134 (109-218)*  [42] | 150 (97-168)*  [15] |
| Tyrosine (34–151)  2 wks to < 19 yrs | 108 (78-161)  [33] | 131 (114-189)*  [14] | 97 (65-142)  [8] | 101 (68-121)*  [0] |
| Valine (128 – 361)  2 wks to < 13 yrs | 137 (117-183)  [17] | 142 (122-148)  [29] | 131 (106-162)  [42] | 133 (102-161)  [38] |
| 1methylhistidine  (1-30) 2 wks to <19yrs | 4 (4-7)  [0] | 4 (4-10)  [0] | 6 (3-8)  [0] | 4 (4-8)  [0] |
| 3methylhistidine  (4-18) 1 wk to < 1 yr | 4 (2-6)  [44] | 3 (2-4)  [80] | 3 (3-4)  [58] | 3 (2-3)  [86] |

* p<0.05 PBMF vs PHMF by Mann Whitney

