# Study summary

This is a protocol for an Investigator Initiated trial, commercially part-funded, non-blinded, randomised controlled trial comparing two nutritionally equivalent methods of breastmilk fortification in healthy preterm infants. The dietary regimes involve fully supporting mothers to provide their own expressed breast milk and using donor human milk to make up shortfall in breastmilk supply. The primary outcome is the level of inflammatory markers in the stool. Parents of infants on neonatal units (Newcastle upon Tyne, Middlesbrough and Southampton) will be approached by clinical team members, and infants will be enrolled after signed informed consent. The study starts when infants are stable and tolerating full milk feeds and finishes prior to hospital discharge and will last for around 3-6 weeks per baby on average.

| Title (Acronym) | **PUFFIN – Preterm Milk Fortification in Neonates** |
| --- | --- |
| Study centres | Ward 35, Royal Victoria Infirmary, Newcastle upon Tyne (lead site)  James Cook University Hospital, Middlesbrough  University Hospital Southampton |
| Study objectives | To compare two comparable methods of fortifying mother’s own breastmilk and/or donor human milk |
| Study design | Randomised, minimised, open label, controlled trial |
| Study population | Inclusion criteria   - Stable preterm infants born <32 completed weeks of gestation or <1500g birthweight tolerating full milk feeds for at least 24 hours - Written informed consent from parents - Maternal intention to continue providing breastmilk - Agreement to use breast milk fortifier   Exclusion criteria   - Parents unwilling to consent - Exposure to formula milk or breastmilk fortifiers before randomisation - Known congenital anomaly affecting the GI tract (gut) - Previous gut surgery or diagnosis of necrotising enterocolitis (NEC) |
| Interventions | Standard commercially available breastmilk fortifier derived from bovine source added to breast milk (control) compared to commercially available fortifier derived from human milk (intervention) |
| Duration | From full milk feeds until fortifier no longer required, or 36 weeks corrected gestation (whichever is earlier) |
| Target number of patients | 36 infants with complete sampling (18 infants per trial arm): recruitment of up to 50 infants may be needed to achieve this |

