## Proposed study to compare two nutritionally equivalent fortifiers

The Puffin study is designed to compare two nutritionally equivalent dietary approaches, by comparing the use of standard cow milk fortifiers (CMBF, control) to that of using human milk fortifier (HMBF, intervention).

- **Setting**: Three tertiary level NICUs
- **Population**: preterm infants <32 weeks or <1500g tolerating milk feeds
- **Control**: use of CMBF from full feeds (tolerating 150mls/kg/day for 1-2 days)
- **Intervention**: use of HMBF from full feeds
- **Primary outcome**: stool inflammatory markers (calprotectin) after 3 weeks exposure
- **Study design**: non-blinded randomised controlled trial
- **Timeframe**: until 36 weeks corrected gestation or when fortifier no longer required whichever is earlier

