### Additional secondary outcomes – growth and neonatal outcomes

We will collect a range of relevant secondary outcomes:

1. Growth – weekly weight, length and head circumference, absolute changes (g/kg/day and mm/week) and change in standard deviation score based on UK reference data from study enrolment until 36wca and/or discharge
2. Episodes of NEC, sepsis - confirmed and clinically suspected according to existing nationally agreed case definitions
3. Chronic lung disease, Retinopathy of prematurity (ROP), Intraventricular haemorrhage, Cystic PVL etc.
4. Days of intensive, high and low dependency care; age at discharge, total length of stay
5. Age at starting fortifier; tolerance, days not received due to intolerance, duration of breastfeeding; type of feeding at discharge (direct breast feeding, tube feeding etc.) etc.
6. Blood/urine work, serum biochemistry and other inflammatory and immune markers (blood and urine): hsCRP, lymphocyte subsets, plasma amino acids (PAA), where samples and funding allow

|  | Enrolment (baseline) | Day 7 | Day 14 | Day 21 | 36w or discharge | Total per infant |
| --- | --- | --- | --- | --- | --- | --- |
| Growth | x | x | x | x | x | 5 |
| Calprotectin | x | x | x | x |  | 4 |
| Stool cytokines |  | x |  | x |  | 2 |
| Stool 16s RNA | x | x |  | x |  | 3 |
| Stool sIgA | x | x |  | x |  | 3 |
| Urine inflammatory/ oxidative measures | x | x | x | x | x | 5 |
| Feeding tolerance etc. | x | x | x | x | x | 5 |
| Targeted bloodwork (PAA etc) |  | x |  | x |  | 2 |
| Clinical outcomes / safety | x | x | x | x | x | 5 |

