### Sample size and Power

We hypothesise that use of a HMF will result in lower levels of fecal calprotectin, and a panel of fecal cytokines and that this will also be associated with greater abundance of Bifidobacteria using 16s gut microbiota analysis. Calprotectin levels in preterm infants vary depending on the presence of neonatal disease but are typically between 4 and 6±2mg/dL[12]. To determine a 50% reduction in fecal calprotectin levels we will study the primary outcome assessment in 36 infants using 5% significance and power of 80%. Allowing for dropouts and other reasons we aim to recruit between 40-50 infants across three NICU sites.

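### Supplementary Table 2 gives one undirected out-of-range percentage per amino acid and compares the arms only by a p<0.05 star; a low/high split and between-arm differences with intervals would say more, and some printed percentages need checking.

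*Protocol*

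**What the plan says.** Supplementary Table 2 covers 25 amino acids on two days in two arms: 100 cells and 50 between-arm comparisons. Its column heads define the content of each cell as "Median (IQR) [% outside ref range", and each row starts with a reference interval and age band, for example "Histidine (65-113) 2 wks to < 19 yrs". The bracketed percentage "outside ref range" is a single number, not split into low and high. The footnote gives the only comparison of the arms: "p<0.05 PBMF vs PHMF by Mann Whitney". No difference, confidence interval or exact p-value is printed. The column sizes are 12 and 12 infants on day 7, and 7 (control) and 13 (intervention) on day 21.

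Under Additional secondary outcomes, the protocol lists "plasma amino acids (PAA), where samples and funding allow". The Study summary describes the trial as "comparing two nutritionally equivalent methods of breastmilk fortification in healthy preterm infants".

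**The concern.** An infant below the interval and an infant above it count the same in the bracketed percentage. Two arms with similar percentages may therefore differ in what is wrong with them, and the share with low values, which matters for a fortifier, is never printed. The star adds only whether p fell below 0.05. With so few infants, a row without a star is compatible with a large difference, and the table gives no interval to show how large. A percentage that disagrees with the median beside it raises the further question of which figure is right.

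**Working it through.** **1. Can direction be read from the printed quartiles?** Each lower quartile was compared with the lower reference limit, and each upper quartile with the upper limit.

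| Result | Cells |
| --- | --- |
| 0% outside | 16 |
| IQR crosses the lower limit only | 40 |
| IQR crosses the upper limit only | 16 |
| IQR crosses both limits (histidine, control, both days) | 2 |
| Non-zero percentage, neither quartile outside | 26 |
| Total | 100 |

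The main direction is thus readable in 40 + 16 = 56 of 84 non-zero cells. It cannot be read from the quartiles in 26, two of which have an IQR printed in impossible order (alanine control day 21, 238-35; citrulline intervention day 21, 18-16).

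One of the 26 is lysine, control, day 7: interval 102-259, IQR 147-214, 33% outside. If all 12 were measured, 33% is 4 infants. Four low values would pull the lower quartile below 102, and four high values would push the upper quartile above 259. Neither happened, so the four must include at least one low and one high.

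**2. Histidine on day 7 (interval 65-113), assuming 12 measured per arm.**
- Control: median 83, IQR 59-120, 58% = 7/12. Lower quartile 59 < 65 means at least 3 low; upper quartile 120 > 113 means at least 3 high. The seven are a mix.
- Intervention: median 114, IQR 85-144, 50% = 6/12. Median 114 > 113 means at least 6 high, which already uses up the printed 6. On these figures essentially all are high.

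So 58% v 50% look alike but describe different profiles.

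**3. Do the percentages agree with the other figures in the cell?** A median outside the interval puts at least half the infants outside, whatever the denominator. Two cells break this rule:
- Phenylalanine, control, day 7: median 46, lower limit 52, printed 42%.
- Ornithine, intervention, day 7: median 133, upper limit 132, printed 42%. The margin is one unit, so rounding may play a part.

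A quartile outside the interval puts about a quarter outside. At the printed column sizes these cells fall short:
- Valine, control, day 7: lower quartile 117 < 128, printed 17% = 2/12, at least 3/12 expected.
- Glutamine, control, day 7: lower quartile 307 < 332, printed 17% = 2/12, at least 3/12 expected.
- Tyrosine, control, day 21: upper quartile 189 > 151, printed 14% = 1/7, at least 2/7 expected.

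Some percentages also match no whole number out of the column size: 88% of 12 (10/12 = 83%, 11/12 = 92%), 80% of 7 (5/7 = 71%, 6/7 = 86%), 86% of 13 (11/13 = 85%, 12/13 = 92%). Denominators seem to vary by amino acid without being stated.

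**4. What does a missing star mean?** Six of the 50 comparisons are starred and 44 are not. Power of the two-sided 5% Mann-Whitney test, simulated on normal data with a pure shift (4,000 runs; two-sided and normal are assumptions):

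| Infants | 1-SD shift | 1.5-SD shift |
| --- | --- | --- |
| 12 v 12 | about 61% | – |
| 7 v 13 | about 48% | about 82% |

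The approximate half-width of a 95% interval for the difference is t × √(1/n1 + 1/n2), in SD units:
- Day 7: 2.074 × √(1/12 + 1/12) = 0.85 SD.
- Day 21: 2.101 × √(1/7 + 1/13) = 0.98 SD.

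Lysine on day 21 illustrates the point. The medians are 159 (control) and 72 (intervention, below the limit of 102), the IQRs are 73-195 and 62-207, and there is no star. The printed figures establish neither a difference nor similarity.

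The protocol's only design calculation, "in 36 infants using 5% significance and power of 80"%, concerns calprotectin; there is no planned figure for amino acids to reproduce.

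**The case against.** The best defence is that the percentage does not stand alone. Median and IQR are printed beside the reference interval, so a shortfall is often visible: the low lysine median on day 21 is read straight from its cell, and the percentages there (43% v 59%) point the same way. The histidine contrast can also be seen from its medians and IQRs. This stands, and it limits the point to the 26 unreadable cells and to the missing share of low values.

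The defence also notes that the histidine split relies on the printed median and percentage agreeing, when ornithine in the same column shows they may not. That stands too, so the intervention arm should be called apparently, not certainly, high. The conflict is itself a reason to re-tabulate.

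Three stronger readings are tempting but unsupported:
- A reader might infer that deficiency in one arm is being passed off as excess in the other. No row shows pure deficiency against pure excess at similar percentages; histidine, mixed against high, is the nearest.
- A reader might infer that the authors take an unstarred row as equivalence. No part of the protocol does so. Where it says "The Puffin study is designed to compare two nutritionally equivalent dietary approaches", equivalence is a premise about the diets.
- A reader might blame the out-of-range rates, which average 37.3%, 34.8%, 33.7% and 35.9% over the 25 amino acids in the four columns, on intervals taken from older children. Every age band starts at or before one month and ten of the 25 end before one year. One can say only that many bands are broad (2 weeks to under 19 years) and none is labelled preterm.

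Finally, this is a descriptive supplementary table and no planned method is breached. That is why the point is minor.

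**Conclusion.** The point holds as a modest reporting weakness. The percentage hides direction in 26 of 84 non-zero cells and makes at least one pair of different profiles look alike. Two percentages contradict their own medians, several others do not fit their quartiles or column sizes, and a missing star carries little information at about 60% (day 7) or 50% (day 21) power for a 1-SD shift. The power figures assume normal data, a pure shift, a two-sided test and full column sizes; smaller denominators would lower them. The histidine split assumes all 12 infants per arm were measured. A full low/high split cannot be derived here because individual values are not printed. Nothing in this touches the trial design, the sample size or the calprotectin analysis.

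**What to change.** Rebuild Supplementary Table 2 from the data held:
- For each amino acid, arm and day, print the percentage below and the percentage above the reference interval, with the number of infants measured.
- Check these against the medians and quartiles, and correct whichever figure is wrong, starting with phenylalanine (control, day 7), ornithine (intervention, day 7) and the two IQRs in impossible order.
- Replace the star by the Hodges-Lehmann difference between arms with its 95% interval.
- Do not add a note that the intervals come from older children. At most, state that many are broad age bands and none is labelled preterm.

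The cost is re-tabulation, with no new samples or assays. The downside is a wider table with wide intervals, which is a fair picture of what 12 v 12 and 7 v 13 infants can show.

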# Study summary

This is a protocol for an Investigator Initiated trial, commercially part-funded, non-blinded, randomised controlled trial comparing two nutritionally equivalent methods of breastmilk fortification in healthy preterm infants. The dietary regimes involve fully supporting mothers to provide their own expressed breast milk and using donor human milk to make up shortfall in breastmilk supply. The primary outcome is the level of inflammatory markers in the stool. Parents of infants on neonatal units (Newcastle upon Tyne, Middlesbrough and Southampton) will be approached by clinical team members, and infants will be enrolled after signed informed consent. The study starts when infants are stable and tolerating full milk feeds and finishes prior to hospital discharge and will last for around 3-6 weeks per baby on average.

| Title (Acronym) | **PUFFIN – Preterm Milk Fortification in Neonates** |
| --- | --- |
| Study centres | Ward 35, Royal Victoria Infirmary, Newcastle upon Tyne (lead site)  James Cook University Hospital, Middlesbrough  University Hospital Southampton |
| Study objectives | To compare two comparable methods of fortifying mother’s own breastmilk and/or donor human milk |
| Study design | Randomised, minimised, open label, controlled trial |
| Study population | Inclusion criteria   - Stable preterm infants born <32 completed weeks of gestation or <1500g birthweight tolerating full milk feeds for at least 24 hours - Written informed consent from parents - Maternal intention to continue providing breastmilk - Agreement to use breast milk fortifier   Exclusion criteria   - Parents unwilling to consent - Exposure to formula milk or breastmilk fortifiers before randomisation - Known congenital anomaly affecting the GI tract (gut) - Previous gut surgery or diagnosis of necrotising enterocolitis (NEC) |
| Interventions | Standard commercially available breastmilk fortifier derived from bovine source added to breast milk (control) compared to commercially available fortifier derived from human milk (intervention) |
| Duration | From full milk feeds until fortifier no longer required, or 36 weeks corrected gestation (whichever is earlier) |
| Target number of patients | 36 infants with complete sampling (18 infants per trial arm): recruitment of up to 50 infants may be needed to achieve this |
| Randomisation | Minimisation using gestation (<28 weeks yes/no) and hospital site. Twins and triplets will be allocated to same study arm. Secured, password protected web-based randomisation using minimisation algorithm ([www.sealedenvelope.com](http://www.sealedenvelope.com) or similar) |
| Primary outcomes | Stool inflammatory marker (calprotectin) |
| Secondary outcomes | Fecal cytokine levels  16s gut microbiota profile  sIgA in stool  Urinary inflammatory markers (iFABP and similar)  Feed tolerance and growth-related outcomes  Neonatal morbidities and clinical outcomes |
| Duration of trial intervention | 36 weeks postmenstrual age or when fortifier no longer required (whichever earlier) |
| Duration of study | Recruitment period: 12 months  Total trial duration: 15 months |
| End of Trial | Discharge from neonatal unit |
| Safety assessments | Routine assessments until discharge from Neonatal Unit  Safety tracking during hospitalisation |

## Introduction

Around 10% of all babies are born premature, but whilst the majority do not require specialist medical treatment, those born very preterm (VPT, <32 weeks’ gestation) require prolonged hospital stay including intensive care. Survival in these VPT infants has increased dramatically in recent years, but death is still common (~10% overall) as are the consequences of life-long physical and cognitive impairment.[1] In the UK around 10,000 VPT infants are born every year, representing an annual cost to the NHS of ~£3 billion.[2] The commonest cause of death or serious illness in preterm infants after the first few days are gut complications such as necrotising enterocolitis (NEC) or septicaemia.[3] Morbidity and mortality is lower in infants who receive mother’s own expressed breastmilk (MOM) and around 90% of mother’s provide at least some breastmilk. When there is a shortfall in MOM supply, an alternative milk is needed, which is either formula milk, or pasteurised, donated, human milk (DHM).[4,5]

A further challenge arises because human breast milk alone will not meet the nutrient requirements of most VPT infants.[6] To meet the higher nutrient requirements of VPT infants, commercially produced breast-milk-fortifiers are milk-powdered products added to mothers’ own milk or donor human milk.[6] These increase the energy and protein density of the milk (along with additional micronutrients, vitamins etc.) and have been routinely used in neonatal units for the last 20-25 years. Most currently used fortifiers are derived from bovine sources (cow milk fortifier, CMF) and are therefore a similar product to cow’s milk infant formula. Whilst routine use of CMF appears to be very safe, there are concerns that using bovine products may increase the risk of allergy, cow milk protein intolerance or other inflammatory problems in preterm infants,[7] however without using CMF most preterm infants will not grow adequately. Poor growth in VPT infants is an important concern because it is strongly linked to worse longer-term cognitive outcomes and may dissuade the mother from continuing to provide breastmilk.[8]

Human milk-derived fortifiers (using donated human breastmilk) have been developed over the last few years and have been widely used in the US for more than 10 years.[9] These have the advantage of avoiding exposure to bovine proteins, and may provide a more optimal balance of nutrients (especially fatty acids and human milk oligosaccharides), but have only been available as a frozen concentrated liquid which makes logistics and transport more complex and these products are consequently more expensive than standard bovine sourced CMF.[9] More recently, human-milk-derived fortifiers have been developed as powders, meaning they are available at a lower cost and do not displace a volume of mother’s own breastmilk (a problem of using a liquid based fortifier, which can be significant at higher doses). Whilst even powdered HMF will be much more expensive than CMF, the additional expense may be justified if these improve longer term infant outcomes. As an initial study, we want to determine if there are any measurable differences in levels of gut inflammation between breastmilk fortifiers derived from cow milk sources (cow milk based fortifier (CMBF), standard, control) to fortifiers derived from human milk (human milk based fortifier (HMBF), intervention).

